# Leukocyte- and platelet-rich fibrin in endoscopic endonasal skull base reconstruction: study protocol for a multicenter prospective, parallel-group, single-blinded randomized controlled non-inferiority trial

**DOI:** 10.1186/s13063-023-07492-w

**Published:** 2023-07-31

**Keywords:** Cerebrospinal fluid leakage, Endoscopic endonasal transsphenoidal approach, Dura, Regenerative medicine, Skull base, Prevention, Leukocyte- and platelet-rich fibrin

## Abstract

**Background:**

Recent advances in endoscopic endonasal transsphenoidal approaches (EETA) for skull base lesions have resulted in a significant increase in extent and complexity of skull base defects, demanding more elaborate and novel reconstruction techniques to prevent cerebrospinal fluid (CSF) leakage and to improve healing. Currently, commercially available fibrin sealants are often used to reinforce the skull base reconstruction. However, problems have been reported regarding hypersensitivity reactions, efficacy, and costs. This trial aims to investigate autologous leukocyte- and platelet-rich fibrin (L-PRF) membranes as an alternative for commercially available fibrin glues in EETA-related skull base reconstruction reinforcement.

**Methods/design:**

This multicenter, prospective randomized controlled trial aims to demonstrate non-inferiority of L-PRF membranes compared to commercially available fibrin sealants in EETA cases (1) without intra-operative CSF-leak as dural or sellar floor closure reinforcement and (2) in EETA cases with intra-operative CSF-leak (or very large defects) in which a classic multilayer reconstruction has been made, as an additional sealing. The trial includes patients undergoing EETA in three different centers in Belgium. Patients are randomized in a 1:1 fashion comparing L-PRF with commercially available fibrin sealants. The primary endpoint is postoperative CSF leakage. Secondary endpoints are identification of risk factors for reconstruction failure, assessment of rhinological symptoms, and interference with postoperative imaging. Additionally, a cost-effectiveness analysis is performed.

**Discussion:**

With this trial, we will evaluate the safety and efficacy of L-PRF compared to commercially available fibrin sealants.

**Trial registration:**

ClinicalTrials.gov NCT03910374. Registered on 10 April 2019.

**Supplementary Information:**

The online version contains supplementary material available at 10.1186/s13063-023-07492-w.

## Administrative information

We used the Standard Protocol Items: Recommendations for Interventional Trials (SPIRIT 2013) checklist when writing our report [1]. The numbers in curly brackets in this protocol correspond to the SPIRIT checklist item numbers.

## Date and version identifier {3}

**Table Tabb:** 

**Date**	**Version**
16-5-2018	Original (v1)
30-8-2018	Amendment no.1: Sample size recalculation (v3)
5-2-2020	Amendment no.2: Addition of ICF translated in English
17-3-2020	Digital follow-up possible (COVID-19 restrictions)
8-5-2020	Amendment no. 3: Addition of ICF translated in French
30-3-2021	Amendment no. 4: Addition of quality control measures (v4)
30-6-2022	Amendment no. 5: Addition of a third participating center: UZ Gent (v5)

## Background and rationale {6a}

The endoscopic endonasal transsphenoidal approach (EETA) to the skull base is a minimally invasive surgical technique that is used to treat a wide range of conditions affecting the skull base, such as pituitary tumors, suprasellar tumors and other diseases of the skull base. EETA is performed through the nasal cavity, without the need for an open craniotomy or facial incision, which leads to a faster recovery, reduced postoperative pain, and a lower risk of complications. However, the nasal cavity is a delicate and complex area that requires precise surgical techniques and can be susceptible to bleeding and inflammation. Additionally, recent advancements in endoscopic endonasal approaches (EEA) for skull base lesions have resulted in a significant increase in the extent and complexity of skull base defects, demanding more elaborate and novel reconstruction techniques to improve healing and prevent reconstruction failure. One major complication of EETA is postoperative cerebrospinal fluid (CSF) leakage. Our recently published systematic review, summarizing data from 113 studies, showed an average postoperative CSF leakage rate of 4.1% in endoscopic transsphenoidal surgeries [2]. A well-known risk factor for postoperative CSF leak is the presence of intraoperative leakage, in case of malignancy or, in cases where a thinned arachnoid herniates into the sella. As the pituitary is located in the diaphragma sellae, a double fold of the dura, large tumors may extend through the central opening of the diaphragm, resulting in a typical dumbbell shape, with an increased risk of CSF leak.

Postoperative leaks may require revision surgeries and/or external CSF drainage. Adequate dural closure is necessary to prevent CSF leak-related complications such as infections and intracranial hypotension. Currently, commercially available fibrin sealants, including Tisseel® and Tachosil®, are considered the gold standard for reinforcement of dural closure, due to their hemostatic, adhesive, and sealant properties [3]. However, problems regarding efficacy, cost, and safety have been reported [4, 5]. As such, commercially available fibrin sealants are expensive and may risk inducing hypersensitivity reactions.

Leukocyte- and platelet-rich fibrin (L-PRF) is a biologically active material that is derived from the patient’s own blood [6]. L-PRF can be prepared in solid form as membranes or as plugs, or as a liquid. The main advantage of L-PRF is that it is completely autologous, thereby minimizing the risk of immunological reactions. Additionally, L-PRF is non-invasive, inexpensive, and can be prepared in a 20-min time span. Solid L-PRF is obtained by centrifuging a small sample of blood for 12 min at 400 g in glass or silica-coated tubes (Fig. 1), during which the coagulation cascade is initiated, and different blood components are separated. The resulting blood clot is the actual L-PRF, situated right above the red blood cell layer. It is in fact a fibrin matrix that contains a high concentration of platelets, leukocytes, and growth factors. These growth factors would promote tissue healing and reduce inflammation, which makes L-PRF an attractive option to use in a variety of surgical procedures. Analogously, liquid L-PRF glue can be prepared in plastic-coated tubes. Because of the hydrophobic surface and shorter centrifugation time (3 min), the product maintains its native fibrinogen and only coagulates in contact with other tissues [7].

**Fig. 1 Fig1:**

Leukocyte- and platelet-rich fibrin (L-PRF) preparation protocol. Membrane preparation after blood collection in glass tubes and centrifugation for 12 min (400 g), compression of the fibrin clot

Recently, platelet concentrates including L-PRF are of increasing interest in EETA to enhance surgical outcomes, improve tissue healing and minimize postoperative bleeding. Regarding postoperative CSF leakage, some preliminary retrospective clinical studies showed comparable results of L-PRF with commercially available fibrin sealants [8–10]. The fibrin matrix of L-PRF has been shown to provide a scaffold for new tissue growth which, in combination with the local release of growth factors from leukocytes and platelets, would promote angiogenesis resulting in improved healing [11, 12].

The preparation of L-PRF is a relatively simple process that can be performed in the operating room in parallel with the surgery. Solid L-PRF membranes in EETA can be applied in different ways, depending on the size and complexity of the lesion. For example, L-PRF with a nasoseptal flap, abdominal fat grafts, or (allogenic or autologous) fascia lata are possible combinations. The application of liquid L-PRF is less interesting in EETA, because of the vertical surgical plane and required coagulation time. The indications for the use of L-PRF are still being defined and need further investigation. In this study, we aim to investigate L-PRF membranes as an alternative to commercially available fibrin sealants for dural closure after EETA.

## Objectives {7}

The general aim of this study is to evaluate the potential of L-PRF in dural closure reinforcement in endoscopic endonasal skull base reconstruction. We aim to show non-inferiority of L-PRF compared to the current standard practice. In addition, we want to demonstrate that L-PRF is more cost-effective than standard commercially available fibrin sealants. Risk factors and possible complications will be evaluated to validate safety.

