### Outcomes {12}

The primary end point is the success rate of both techniques at 3 months postoperative, which means the absence of CSF leak that needs surgical revision or any other intervention e.g., lumbar drainage, repeat imaging, or longer hospitalization. Success rate in both groups will be reported in proportions with a 95% confidence interval.

Secondary endpoints include identification of potential risk factors for reconstruction failure, assessment of potential interference of reconstruction material with post-operative imaging, analysis of the effect of the treatment on quality of life (QoL), and post-operative rhinological symptoms. Rhinological symptoms are assessed based on specific validated questionnaires, i.e. visual analog scale (VAS) (for runny nose, nasal itches, sneezing, nasal congestion, facial pain, headache, loss of smell), Sino-Nasal Outcome Test-22 (SNOT-22) and Skull Base Inventory (SBI).

The outcomes will be assessed at six study visits within a time frame of 1 year (Table 2), and a comparison will be made between the two groups considering the change to baseline (preoperative visit). Data will be presented as mean and standard deviation or median and interquartile range for continuous variables (including VAS score, SBI score, SNOT-22 score) or as proportions with 95% confidence intervals for categorical variables (intraoperative leak, complications, surgical indication, or type of tumor).

**Table 2 Tab2:** Outcome assessment

**Procedure**	**Visit 1** *Screening*	**Visit 2** *Allocation*	**Visit 3** *FU1*^a^	**Visit 4** *FU 2*^b^	**Visit 5** *FU 3*^c^	**Visit 6** *FU 4*^d^

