### Sample size {14}

Sample size calculation was performed according to the primary outcome, using an online power calculator for binary outcome non-inferiority trials (Sealed Envelope Ltd. Available from: https://www.sealedenvelope.com). This is a non-inferiority trial with a binary outcome using a one-sided alpha 0.05 and 80% power. The assumed success rate is 94.3% in the control arm, based on center-specific experience as well as the literature [14]. Data on the use of L-PRF for this indication is limited, but we assume a 95% success rate based on prior feasibility studies [8–10].

The statistical hypothesis for testing the treatment difference is presented as follows; H_0_: Δ ≤  − 0.07 tested against the alternative hypothesis H_A_: Δ >  − 0.07, where Δ is the difference between the success rates of experimental and control condition and − 0.07 is the non-inferiority difference. The non-inferiority limit was set at 0.07 considering (a) reported CSF leakage rates without commercially available fibrin sealant averaging 17.2% [15] and (b) important additional benefits of L-PRF compared to commercially available fibrin sealants including the completely autologous nature (eliminating immune reactions), presence of immunologic cells and reduced costs.

Based on this power calculation, 212 patients need to be included, 106 in each group. In order to account for potential missing follow-up information, failure of L-PRF preparation, or non-adherence to the allocation (expected drop-out rate less than 2%), 220 subjects will be enrolled, 110 in each group.

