## Statistical methods

### Statistical methods for primary and secondary outcomes {20a}

Data will be analyzed in GraphPad Prism software using a simple *t*-test, or nonparametric Mann–Whitney *U* test when not normally distributed, with Bonferroni Holm correction for multiple testing. A *p*-value ˂0.05 is considered statistically significant. The primary outcome, i.e., CSF leakage, will be analyzed in terms of a difference in risk between the two treatment groups. The mean difference between the two treatment groups will be reported as a 95% confidence interval. Secondary endpoints are calculated using simple *t*-test, or nonparametric Mann–Whitney *U* test when not normally distributed, or Fisher’s exact test or chi-squared test, based on the number of events.

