### Adverse events reporting and harms {22}

Harms and adverse events that may be expected in the study population include diabetes insipidus, anterior pituitary insufficiency, and nasal septum perforation. During hospitalization, harms will be systematically collected from documentation of clinical and radiological examinations, and daily nursing reports in the electronical patient files. At the outpatient follow-up visits (FU1-4), harms will be collected based on anamnesis and clinical examination. Additionally, three open-ended questions will be presented to the subjects:Did you suffer from any complaints?Have you been ill?Have you taken any medication?

During the study, all adverse events are recorded and notified to the sponsor in an annual progress report. In agreement with the local law, serious adverse events are reported immediately, after first knowledge, to the sponsor and ethical committee, accompanied by detailed written reports. A serious adverse event is defined as any untoward medical occurrence or effect that results in death, is life-threatening, requires hospitalization or prolongation of existing hospitalization, results in persistent or significant disability or incapacity, or is a congenital anomaly or birth defect. Such serious adverse events will be reported in the final manuscript of the study. The sponsor shall keep detailed reports of all adverse events which are reported. For reported death of a subject, the investigator shall supply the institutional Ethical Committee with any additional information requested.

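### The aim to validate safety has no margin or between-arm interval behind it for harms other than CSF leak, and a non-significant equality test at 110 per arm cannot supply that validation

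*Protocol article*

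**What the plan says.** All references are to the protocol article.

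- **Aim.** Objectives {7}: "Risk factors and possible complications will be evaluated to validate safety". No criterion for that validation is attached.
- **Descriptive reporting.** Outcomes {12} presents data "as proportions with 95% confidence intervals for categorical variables (intraoperative leak, complications, surgical indication, or type of tumor"). Complications share that list with surgical indication and tumor type.
- **Between-arm tests.** Statistical methods {20a} opens with t-tests or Mann–Whitney tests "with Bonferroni Holm correction for multiple testing" and a general threshold: a p-"value ˂0.05 is considered statistically significant". Secondary endpoints are then tested with the same methods "or Fisher’s exact test or chi-squared test, based on the number of events". An interval for the difference between arms is stated for the primary outcome only.
- **Margin.** Sample size {14} sets 0.07 for the CSF-leak success rate and for nothing else: "This is a non-inferiority trial with a binary outcome using a one-sided alpha 0.05 and 80% power".
- **Harms.** Adverse events {22}: "Harms and adverse events that may be expected in the study population include diabetes insipidus, anterior pituitary insufficiency, and nasal septum perforation". It also describes systematic collection of harms and reporting of serious adverse events, but no comparison between arms.

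**The concern.** To validate safety is to claim that a relevant excess of harm has been ruled out. Ruling out an excess needs an upper bound on the difference between arms, set against a stated limit or at least reported and interpreted. For CSF leak the protocol does this. For other complications the only between-arm tool in the article is a test of the hypothesis that the arms are equal. Failing to reject that hypothesis does not show that the arms are alike, least of all in a sample sized for another question.

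A multiplicity correction adds to the problem if it covers harms. Holm guards against declaring differences that are not there. For harms the costlier error is to overlook a difference that is there, and each added test raises the bar for the smallest p-value.

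At stake is what the trial may conclude about L-PRF beyond CSF leak. A significant test can raise an alarm, but the plan has nothing that could support the positive statement the objective promises.

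**Working it through.** **Inputs.** From Sample size {14}: 106 per arm required, 110 per arm enrolled, control success 94.3%, L-PRF success 95%, margin 0.07, one-sided alpha 0.05, power 80%. From Statistical methods {20a}: p<0.05 (taken as two-sided, since sidedness is not stated), Fisher or chi-squared. Complication rates are assumptions, because the protocol gives none.

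**Step 1. Reproduce the protocol's own figure.** With unpooled variance,

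n per arm = (z₀.₉₅ + z₀.₈₀)² × [p_C(1−p_C) + p_T(1−p_T)] / (p_T − p_C + margin)²

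= 6.183 × (0.943×0.057 + 0.95×0.05) / (0.007 + 0.07)²

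= 6.183 × 0.10125 / 0.005929 = 105.6, so 106 per arm and 212 in total.

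This matches. The sample was sized for CSF leak alone.

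**Step 2. Power of the equality tests for a complication.** At 110 per arm, power is the sum of the binomial probabilities of all pairs of counts in which the test rejects and L-PRF has more events:

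Power = Σ Bin(a; 110, p_T) × Bin(b; 110, p_C), over pairs with a > b and p-value < alpha.

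| Control vs L-PRF (assumed) | Fisher, power (missed) | Chi-squared, power (missed) |
|---|---|---|
| 5% vs 10% | 0.214 (79%) | 0.298 (70%) |
| 5% vs 12% | 0.378 (62%) | 0.480 (52%) |
| 10% vs 17% | 0.265 (73%) | 0.337 (66%) |
| 5% vs 15% | 0.641 (36%) | 0.727 (27%) |
| 5% vs 20% | 0.914 (9%) | 0.944 (6%) |
| 10% vs 25% | 0.804 (20%) | 0.849 (15%) |

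All at alpha 0.05, with no Holm penalty. Rows 2 and 3 are 7-point excesses. That size is borrowed from the CSF-leak margin as a yardstick; the protocol does not apply it to other harms.

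**Step 3. If Holm did cover harms.** As an illustration only, take the three harms named in Adverse events {22} as the family. The first Holm step is then 0.05/3 = 0.0167. Fisher power for the first three rows falls to 0.099, 0.218 and 0.144, so the misses rise to 90%, 78% and 86%. The protocol does not define such a family.

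**Step 4. What a difference interval would show.** Suppose 11/110 on L-PRF and 6/110 on control. Fisher gives p = 0.31. The 95% Newcombe interval for the difference runs from −2.8 to +12.2 percentage points. The test says only that the result is not significant. The interval says that an excess of up to about 12 points has not been excluded.

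**The case against.** **Complications are not left to tests alone.** Outcomes {12} plans 95% intervals for their proportions, Adverse events {22} provides for systematic collection and for publication of serious adverse events, and a supervisory committee reviews patient safety annually. This stands, and it would be wrong to say that only Holm-corrected tests lie behind the safety aim. But an interval for a proportion is not an interval for the difference between arms, and collection and review supply no between-arm inference.

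**Holm may not apply to harms.** The correction is attached to the sentence on t-tests and Mann–Whitney tests, and complications are not among the secondary endpoints listed in Outcomes {12}. The text is ambiguous, and that ambiguity is a reason to settle it in one sentence. The misses in Step 2 do not depend on Holm.

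**Nobody says that non-significance means safe.** A reader might infer that a harmful arm would usually be declared safe. The document does not support that. It contains no such rule, the abstract and Discussion speak more modestly of evaluating and assessing safety, and large excesses would usually be detected. What remains is that the article offers no other between-arm route to the validation its objective names.

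**Fisher is the less favourable test.** The choice depends on the number of events, with no cut-off given. At the rates in the first three rows, expected counts are about 8 or more per arm, so by the usual convention chi-squared would apply and its lower miss rates would be the relevant ones. Fair; hence both are shown.

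**This is detail for the analysis plan, and most trials lack power for individual harms.** How adverse events are tabulated can be left to an analysis plan that is not shown. The wording of the objective and the general Holm statement cannot, because this document fixes them. Low power for harms is ordinary; an aim to validate safety is what makes it matter here.

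**Conclusion.** The point holds in limited form. CSF leak, the principal complication, has its own powered non-inferiority test and is not in question. For all other harms the stated aim exceeds what the described methods can deliver. Moderate excesses are often missed: 70–79% of trials for 5% against 10%, and 52–73% for a 7-point excess, across the two tests and before any Holm step. Excesses of about 15 points are mostly caught, with Fisher power of 0.91 for 5% against 20% and 0.80 for 10% against 25%.

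These figures rest on assumed complication rates, 110 analysed per arm and two-sided testing. Which excess counts as relevant is not stated in the protocol, so the finding cannot be put as missing most relevant excesses. The conclusion that a non-significant test does not validate safety does not depend on the particular rates chosen. The change is worth making before analysis, because it decides what the trial may say about safety.

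**What to change.** 1. **Objectives {7}.** Replace the aim of validating safety with a statement that the trial estimates the between-arm excess risk of complications. Add that a non-significant test is not evidence of safety.
2. **Outcomes {12} and Statistical methods {20a}.** For the harms named in Adverse events {22} and for serious adverse events, report the risk difference, L-PRF minus control, with an unadjusted 95% score-type interval (Newcombe or Miettinen–Nurminen). Interpret its upper limit as the largest excess that the data do not rule out.
3. **Statistical methods {20a}.** State that the Bonferroni-Holm correction does not apply to complications and adverse events.

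**Cost.** Wording in the protocol and analysis plan only; no additional patients or data. The safety statement will be less favourable than the present aim suggests, and uncorrected comparisons of harms will give more nominal false alarms.

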### Trial design {8}

This study is a multicenter, single-blinded, prospective randomized controlled trial with subjects randomized 1:1 in two parallel groups, i.e., experimental (L-PRF treatment) and active control (commercially available fibrin sealants).

In this study, the general objective is to show non-inferiority of L-PRF as a closure technique compared to commercially available fibrin sealants in endoscopic transsphenoidal surgery. This prospective randomized controlled trial was approved by the local Ethical Committee (UZ Leuven (S61636), AZ Sint-Jan Brugge, UZ Gent) and is registered at ClinicalTrials.gov (ID: NCT003910374). Recruitment started on 07 November 2018.

